### Wait-list control condition

Participants assigned to the control group will remain on the wait-list during the intervention and follow-up periods and will not receive any specific intervention. To ensure intervention equity, they will be offered access to the full program upon completion of the T2 assessment.

Participants in both groups will be allowed to continue their usual activities and access external health-related services (e.g., psychological support, personal training, or dietary counseling) throughout the study period. To monitor potential sources of contamination, participants will be asked to report any engagement in such services during the study.

These data will be recorded and considered in the interpretation of the findings. If deemed necessary, additional sensitivity analyses will be conducted to explore the potential impact of external interventions on the study outcomes.

All protocol deviations, including non-adherence to the intervention or engagement in external programs, will be documented and reported following established guidelines for randomized controlled trials.

### Measures

Assessments will be conducted at three time points: baseline, post-intervention, and six-month follow-up.

### Primary outcome

The primary outcome of the study will be between-group differences in autonomous motivation toward physical activity at six-month follow-up, assessed using the Behavioral Regulation in Exercise Questionnaire–3 (BREQ-3) [25], validated in the Spanish population [26]. The instrument consists of 23 items distributed across six subscales representing different forms of motivational regulation: amotivation, external regulation, introjected regulation, identified regulation, integrated regulation, and intrinsic motivation. Responses are recorded on a five-point Likert scale ranging from 0 (“Not true for me”) to 4 (“Very true for me”).

From these scores, the Relative Autonomy Index (RAI) will be computed to quantify the overall degree of self-determination in exercise motivation. Higher RAI scores indicate more autonomous forms of motivation, whereas lower scores reflect a predominance of controlled regulation or amotivation. Additionally, following recent meta-analytic recommendations, scores for each of the six subscales will be reported independently to avoid masking potential distinct effects of different regulatory styles on physical activity outcomes [25,27]. The scale has demonstrated a quasi-simplex pattern of associations and high temporal stability in Spanish samples [26].

### Secondary outcomes

Secondary outcomes include psychological and behavioral variables relevant to understanding motivational change. Satisfaction and frustration of basic psychological needs will be assessed using the Basic Psychological Need Satisfaction and Frustration Scale (BPNSFS) [28], a 24-item instrument measuring autonomy, competence, and relatedness, each examined in terms of both satisfaction and frustration dimensions.

Physical activity levels will be measured using the short form of the International Physical Activity Questionnaire (IPAQ-short) [29], which estimates time spent in vigorous and moderate physical activity as well as walking, expressed in MET-minutes per week. Because the BREQ‑3 specifically assesses exercise motivational regulations and the IPAQ‑SF captures general physical activity, both instruments will be used to comprehensively reflect behavioral engagement and its motivational determinants.

Positive body image will be assessed using the Body Appreciation Scale–2 (BAS-2) [30], Spanish adaptation [31], a 10-item Likert-type scale designed to evaluate body acceptance and respect.

Finally, risk of eating disorders will be measured using the Eating Attitudes Test–26 (EAT-26) [32], a widely used instrument in epidemiological and preventive research.

### Administration procedure

Questionnaires will be administered in a predefined order designed to minimize response bias and safeguard participant well-being: first the BPNSFS, followed by the BREQ-3, the IPAQ-short, the BAS-2, and finally the EAT-26, given its more sensitive nature. The estimated completion time for the full assessment battery is approximately 25–35 minutes.

All assessments will be conducted in digital format to ensure accessibility, standardized administration, and data confidentiality.

### Data management

All data collected during the study will be stored on a secure, access‑restricted server hosted by the University. Each participant will be assigned a unique identification code, and all datasets used for analysis will be coded to ensure participant anonymity by removing any direct or indirect identifiers. The correspondence between participant identities and identification codes will be kept in an encrypted, password‑protected file accessible only to the principal investigators. Data entry will be conducted electronically through a secure platform, and regular data quality checks will be performed to detect inconsistencies or missing values. Access to the raw data during the study will be limited to authorized members of the research team who have completed institutional training in data protection and confidentiality. All data management procedures will comply with the European Union General Data Protection Regulation [33] and institutional policies on data protection and research integrity.

Missing data will be handled under an intention-to-treat framework using likelihood-based mixed models for repeated measures (MMRM). This approach incorporates all available observed data without the need for prior imputation and provides valid inferences under the assumption that data are missing at random (MAR). Participants will contribute data up to the point at which observations are available, and no ad hoc imputation procedures will be applied. All datasets and accompanying metadata will be retained for a minimum of five years after publication to allow verification, auditing, or secondary analyses.

### Statistical analysis

All statistical analyses will be pre-specified prior to database lock and conducted using RStudio (v.2026.01.1 + 403, Posit Software). Analyses will follow the intention-to-treat principle, as the primary analytical approach. In addition, per-protocol analyses will be conducted as sensitivity analyses to examine the robustness of findings and to account for potential variations in intervention fidelity (e.g., adherence to the full set of sessions). Descriptive statistics will first be calculated for all study variables, including measures of central tendency and dispersion. Assumptions of normality will be assessed using appropriate statistical tests and graphical methods.

To evaluate the effect of the intervention on the primary outcome, a mixed model for repeated measures (MMRM) will be used, including all post-randomization assessments of autonomous motivation toward physical activity (BREQ-3), Fixed effects will include treatment group (experimental vs. control), assessment time, the treatment-by-time interaction, and baseline values of the outcome as a covariate.

An appropriate covariance structure (e.g., unstructured or alternative based on model fit indices) will be specified to account for within-participant correlations across repeated measurements. The primary endpoint will be the between-group difference at six-month follow-up, while effects at post-intervention will be considered secondary analyses. Least-squares mean differences between groups will be estimated from the model, along with corresponding 95% confidence intervals and p-values. This likelihood-based approach uses all available observed data without imputing missing values and provides valid inferences under the missing at random (MAR) assumption. Secondary outcomes, including satisfaction and frustration of basic psychological needs, physical activity levels, positive body image, and risk of eating disorders, will be analyzed using equivalent MMRM approaches. In cases where parametric assumptions are violated, robust mixed-effects models and bootstrapping procedures will be applied to obtain reliable parameter estimates. Exploratory analyses of the six BREQ‑3 subscales will follow the same mixed‑effects modelling approach. In addition, mediation will be tested with a half-longitudinal model [34]: group is the independent variable, the change in autonomous motivation (BREQ-3 RAI) from T0 to T1 is the mediator, and the changes in physical activity (IPAQ-SF), positive body image (BAS-2), and eating disorder risk (EAT-26) from T1 to T2 are the outcomes. The primary specification is a single-level structural equation model (lavaan) with bias-corrected bootstrap confidence intervals for the indirect effect; a multilevel SEM that accounts for the partially nested delivery subgroups is reported as a sensitivity analysis. Full detail is given in the SAP (see Supporting information S3 File). Statistical significance will be set at p < .05. Effect sizes will be calculated to facilitate interpretation of the magnitude of effects. Ninety-five percent confidence intervals will be reported for all relevant estimates.

To enhance transparency and reproducibility, a complete Statistical Analysis Plan (SAP, v2.0), structured following the template by [35], is provided as supplementary material (S3 File).

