### Randomization, blinding, and allocation

Following baseline assessment, participants will be randomly allocated to either the experimental or the control group in a 1:1 ratio. The allocation sequence will be generated in R using the *blockrand* package by an independent researcher not involved in participant recruitment, intervention delivery or outcome assessment, with a random seed kept confidential until recruitment is complete.

Block randomization will be used, with permuted blocks of variable size (4, 8, and 12) and 1:1 allocation within each block, without stratification given the homogeneity of the target population in age and academic context. Using variable block sizes that are not disclosed to enrolling staff preserves allocation concealment by preventing prediction of forthcoming assignments, while ensuring balanced group sizes throughout recruitment and minimizing selection bias.

Recruiting and enrolling staff remain masked to the allocation sequence and to the (variable) block sizes throughout the trial. As a post-hoc verification of the absence of allocation selection bias, a Berger–Exner test will be applied to check for any association between the allocation sequence and baseline prognostic characteristics.

Due to the nature of the psychoeducational intervention, blinding of participants and intervention providers (facilitators) will not be feasible. Outcome data will be collected using self-administered standardized questionnaires, minimizing assessor-related bias.

Researchers involved in data management and statistical analysis will remain blinded to group allocation until the primary analyses are completed. Data will be coded using anonymized group identifiers to ensure concealment during analysis.

This approach ensures appropriate separation between sequence generation, allocation concealment, and blinding procedures, in accordance with established guidelines for randomized controlled trials.

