#### Experimental intervention.

Participants assigned to the experimental group will take part in a face-to-face psychoeducational program consisting of six 60-minute group workshops, conducted in small groups of up to 15 participants. Each participant remains in the same delivery subgroup across the six sessions. This format facilitates social interaction and the creation of a need-supportive climate, factors identified as relevant in interventions based on Self-Determination Theory (SDT). Sessions are facilitated by trained professionals with experience in exercise science and psychonutrition, who receive standardized training prior to intervention delivery to ensure consistency across groups. Facilitators complete standardized training covering SDT principles, functionality‑based body image strategies, session structure, and fidelity procedures. The intervention includes structured presentation slides, participant worksheets, guided experiential activities, and reflective exercises. Detailed intervention materials are available from the authors upon reasonable request. Minor contextual adaptations (e.g., examples or wording adjustments) may be made, but core intervention components remain unchanged. The intervention will be delivered following a standardized manual based on established SDT techniques, including autonomy support, structure, and involvement [13,14], as summarized in Table 1.

**Table 1 pone.0355374.t001:** Structure, objectives, and Basic Psychological Needs-Supportive Strategies targeted in the intervention workshops.

Workshop	Primary focus	Need-Supportive Strategies (SDT-based)	Basic Psychological Needs targeted
1	Awareness of motivational quality toward PA	Providing a meaningful rationale: explaining the “why” behind PA engagement.	Autonomy
2	Personal values and autonomously chosen goals	Autonomy support: promoting the internalization of PA goals based on personal interests.	Autonomy & Competence
3	Perceived competence and flexible planning	Structure: providing clear guidance, mastery-oriented feedback, and skill-building for PA.	Autonomy & Competence
4	Positive body image from a functionality-oriented perspective	Acknowledging perspectives: validating participants’ feelings and fostering intrinsic values.	Autonomy & Relatedness
5	Social support and supportive relational climate	Involvement: fostering a warm, supportive, and non-judgmental climate for PA.	Relatedness

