Assessments will be conducted at three time points: baseline, immediate post-intervention, and six-month follow-up. To ensure both adherence and intervention fidelity, facilitators will receive prior specific training and follow a structured session guide. Fidelity to the protocol will be monitored by the research team using standardized checklists completed after each workshop. Additionally, a set of retention strategies will be implemented to minimize attrition and missing data, including periodic email reminders and advance notifications of session schedules. Attendance will be systematically monitored throughout the intervention, and participants will be reminded of the importance of continuous participation from the outset to ensure data completeness across all assessment points.

Table 2 presents the standardized pedagogical structure applied in each workshop session, comprising six sequential phases that combine initial welcome, experiential activation, psychoeducational input, group-based activities, individual reflection, and a brief closing synthesis.

**Table 2 pone.0355374.t002:** Standard pedagogical structure of each workshop session.

Session phase	Duration	Description
Welcome and psychological climate	5 min	Facilitators welcome participants, present the objectives of the session, and establish a supportive and non-evaluative group climate
Experiential activation	10 min	Short reflective or experiential activity designed to activate participants’ previous experiences and beliefs related to the workshop topic
Psychoeducational content	15 min	Brief evidence-based explanation of the key concept addressed in the workshop (e.g., motivational regulation, body functionality, social support)
Experiential group activity	20 min	Interactive activities conducted in pairs or small groups allowing participants to apply the concepts through discussion, reflection, or body-awareness exercises
Personal reflection and transfer	5 min	Individual reflection on how the workshop content relates to participants’ own behaviors and experiences
Closing and synthesis	5 min	Summary of key ideas and encouragement to apply the concepts in everyday life

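### An attendance-based per-protocol set selects after randomisation in one arm only, so it should be labelled supportive rather than a robustness check, with a complier-average estimate for the adherence question

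*Protocol article*

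**What the plan says.** The Statistical analysis section of the protocol article sets the hierarchy: "Analyses will follow the intention-to-treat principle, as the primary analytical approach". It then gives the per-protocol analysis two jobs: "per-protocol analyses will be conducted as sensitivity analyses to examine the robustness of findings and to account for potential variations in intervention fidelity". The only indication of how the per-protocol set would be formed is an example, "e.g., adherence to the full set of sessions".

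Three other statements bear on this:

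- The experimental arm is offered "six 60-minute group workshops, conducted in small groups of up to 15 participants" (Experimental intervention).
- Controls "will remain on the wait-list during the intervention and follow-up periods and will not receive any specific intervention" (Wait-list control condition). They are offered the programme only after T2.
- "Attendance will be systematically monitored throughout the intervention" (Experimental intervention), so session counts will exist for everyone allocated to the programme.

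The article states no attendance threshold, no expected attendance and no comparator set for the per-protocol analysis. It refers to an SAP for full detail, which is not at hand.

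**The concern.** A sensitivity analysis tests robustness when it targets the same effect under different but credible assumptions. An attendance-based per-protocol comparison does not do that here. Sessions exist in one arm only, so the criterion filters the experimental arm on behaviour after randomisation and cannot filter the control arm in the same way.

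The behaviour is also plausibly tied to the outcome. The primary outcome is autonomous exercise motivation, and the sessions are workshops about exercise motivation. The article accepts related links elsewhere: the Introduction associates controlled motivation with poorer adherence (to physical activity), and the Discussion allows that those who volunteer may be the more motivated. Adjusting for one baseline RAI score removes only the part of the link that this score captures.

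What is at stake is interpretation. The Sample size section describes power as moderate, approaching adequate in some scenarios. An inconclusive ITT result beside a larger per-protocol estimate is therefore a realistic outcome, and a text that calls the second a robustness check invites reading it as support for an effect.

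**Working it through.** **Inputs from the article.** Six sessions; allocation 1:1; no sessions for controls before T2; 82 per group as the minimum sample; planning effect d of 0.20–0.30. The article gives no figure for attendance or for the per-protocol analysis, so there is none to reproduce on this point. The stated 164 does reproduce: a within-between interaction test with f = 0.10, assuming a within-subject correlation of 0.5, has power 0.805. The checks below use 82 analysed per arm.

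**Assumed inputs, not in the article.** The share *p* attending all six sessions, and the gap *g* in T2 RAI, without treatment and after baseline adjustment, between would-be full attenders and the others.

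**Step 1: bias under a true null.** Suppose full attenders are compared with the whole control arm. By randomisation the control arm contains the same mixture of the two kinds of student, so its adjusted mean is *p*·μ(full) + (1 − *p*)·μ(other). The experimental side retains only μ(full). The difference is

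bias = (1 − *p*) × [μ(full) − μ(other)] = (1 − *p*) × *g*.

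- *p* = 0.80, *g* = 0.2 SD: 0.20 × 0.2 = 0.04 SD
- *p* = 0.70, *g* = 0.3 SD: 0.30 × 0.3 = 0.09 SD
- *p* = 0.60, *g* = 0.4 SD: 0.40 × 0.4 = 0.16 SD
- *g* = 0: bias 0, whatever *p* is

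The middle case is 0.09/0.30 = 30% to 0.09/0.20 = 45% of the planning effect.

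**Step 2: simulation under a true null.** 4,000 runs per cell, baseline–T2 correlation 0.6, T2 comparison adjusted for baseline. The rows vary the correlation between attendance propensity and the baseline-adjusted outcome. Cells show the mean per-protocol estimate in SD and the two-sided rejection rate at 5%.

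| Correlation | 40% attend all | 60% attend all | 80% attend all |
|---|---|---|---|
| 0 | 0.00; 5% | 0.00; 5% | 0.00; 5% |
| 0.2 | 0.16; 16% | 0.10; 12% | 0.06; 7% |
| 0.3 | 0.23; 28% | 0.16; 19% | 0.08; 10% |
| 0.4 | 0.31; 46% | 0.21; 30% | 0.11; 13% |

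Dividing by (1 − *p*) links this to step 1. At 60% attendance, correlations of 0.2 and 0.4 imply gaps of 0.10/0.40 ≈ 0.26 SD (0.104 unrounded) and 0.21/0.40 ≈ 0.52 SD, so the table reaches somewhat beyond the 0.2–0.4 SD range. ITT averaged 0.00 SD with about 5% rejections throughout.

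**Step 3: an allocation-based alternative.** With allocation as the only instrument and no sessions among controls, two-stage least squares on sessions attended gives, up to baseline adjustment,

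six-session effect = 6 × (ITT difference) ÷ (mean sessions attended in the experimental arm).

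Simulated at correlation 0.3, with non-full attenders spread over 0–5 sessions and 40/60/80% attending all six:

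- True null: mean 0.00 SD, rejections about 5%.
- True six-session effect 0.30 SD, linear in sessions: mean 0.30 SD throughout. Per-protocol gives 0.54/0.46/0.38.
- Benefit reaching its ceiling at four sessions: 0.34/0.33/0.31.
- Standard error about 0.14–0.19, against about 0.125 for ITT.

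A binary six-of-six version does worse if partial attenders gain anything. With true effects of 0.30 SD (full) and 0.15 SD (partial), it averages 0.52/0.40/0.34.

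**The case against.** The strongest reply is that the article leaves the details open. A reader might infer that full attenders will be compared with all controls. The text does not say so: full attendance is only an example, and the comparator is not named. Controls could also leave a per-protocol set, since "All protocol deviations, including non-adherence to the intervention or engagement in external programs, will be documented and reported". This stands, and the step 1 figures hold only for the all-controls comparison. It does not rescue the robustness role, because removing controls for using external programmes is a different filter and does not recreate the attenders' counterparts. Nor would an attendance threshold in the SAP cure one-sided selection.

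A reader might also infer that per-protocol must match or exceed ITT whatever the truth. That is unsupported: with no residual link the bias is about zero, and if already active students skip sessions it could run the other way. The article documents neither the sign nor the size of the link.

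A third tempting reading is that a complier-average estimate is free of bias. It avoids the attendance selection but needs allocation to act only through attendance. That is debatable with unblinded participants and self-reported outcomes. It also needs a roughly linear dose effect, although the six workshops differ in content. Run on T2 completers alone, it would give up the primary model's handling of missing data. And because it rescales ITT, it cannot serve as a robustness check either. All of this stands.

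Finally, the lack of a complier analysis in the article is not an error, since the SAP may contain one.

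**Conclusion.** The point holds in limited form. The article itself assigns a robustness role to an analysis that, under its own example, selects in one arm on a behaviour plausibly tied to the outcome. The illustrative bias under a true null is 0.04–0.16 SD, and about zero without a residual link between attendance and T2 RAI. These sizes rest on assumed attendance (60–80%), an assumed gap (0.2–0.4 SD) and the full control arm as comparator.

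The documents do not support a reading that the trial's main conclusion is at risk. The primary mixed model under ITT is untouched, and per-protocol is already placed among the sensitivity analyses. How an inconclusive ITT result would be presented is a matter of conjecture. With the simulated standard error of about 0.125, ITT power is roughly 67% at d = 0.30 and 36% at d = 0.20, so such a result is more likely than not only towards the low end of the planning range. This is a cheap improvement, not a flaw in the primary analysis.

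**What to change.** In the Statistical analysis section:

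1. Stop describing attendance-based per-protocol analysis as a check of robustness. Label it supportive and non-randomised, and state the attendance criterion and the comparator set.
2. For the adherence question, add a complier-average estimate unless the SAP already has one: allocation as instrument for number of sessions attended, baseline RAI as covariate, reported per session and for six sessions. Use the session count rather than six-or-nothing.
3. State its assumptions: allocation affects T2 RAI only through attendance, and the dose effect is roughly linear. Non-compliance is one-sided because controls have no access before T2.
4. Handle missing T2 data consistently with the missing-at-random assumption of the primary model. One route is to divide the model's T2 group difference by mean sessions attended, counting sessions after withdrawal as not attended, with a bootstrap interval.

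The cost is a few lines of SAP text and code on attendance data already to be collected, and the article states that recruitment has not begun. The downsides are a wider interval than ITT, assumptions that cannot be tested from the data, and a result that rescales ITT rather than checking it independently.

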### Sample size

Sample size was initially estimated using a repeated-measures ANOVA framework as an approximation of the planned longitudinal analysis, implemented in G*Power software (version 3.1.9.6). A small effect size was assumed (f = 0.10), consistent with meta-analytic evidence from self-determination theory–based interventions (g ≈ 0.40) [14] and body image programs (g ≈ 0.40) [19].

With a significance level of α = 0.05 and statistical power (1 − β) of 0.80, and assuming two groups with three repeated measurements, the minimum required sample size was estimated to be 164 participants (82 per group). To account for an anticipated attrition rate of approximately 20%, the target sample size was increased to 196 participants.

Given the longitudinal design of the study and the use of mixed models for repeated measures (MMRM) as the primary analytical approach, simulation-based power analyses were subsequently conducted in R to obtain more realistic estimates under plausible assumptions.

These simulations incorporated baseline adjustment, within-subject correlation, and missing data patterns consistent with behavioral interventions. Effect sizes were specified in the small-to-moderate range (d ≈ 0.20–0.30), and assumptions regarding residual variability and within-subject correlation were informed by prior literature on autonomous motivation (RAI).

Power was evaluated with respect to the primary contrast at six-month follow-up time point.

Simulation results indicated that the planned sample size provides moderate, and in some scenarios approaching adequate, statistical power under realistic assumptions, while reflecting the inherent variability associated with behavioral and psychological outcomes.

These complementary approaches ensured both consistency with conventional sample size estimation methods and alignment with the planned analytical model.

To account for potential deviations from the target sample size, contingency strategies were pre-specified. If the final sample exceeds the planned size, all participants will be retained in the analyses to maximize statistical power and precision. If the achieved sample size falls below the target, additional recruitment efforts will be undertaken following the same procedures. Based on the initial assumptions, a minimum sample size of 70 participants per group would still provide adequate statistical power (1 − β = 0.80) to detect moderate effects (g ≈ 0.40).

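### As described, the primary MMRM ignores the fixed workshop groups in the experimental arm; if six-month outcomes correlate within those groups, its standard error is too small

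*Protocol article*

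**What the plan says.** The section on the experimental intervention says that the workshops are "conducted in small groups of up to 15 participants. Each participant remains in the same delivery subgroup across the six sessions". The section on the wait-list control condition gives controls no programme until after the T2 assessment, so they are not grouped. Randomization is individual and 1:1.

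The Statistical analysis section describes the primary MMRM: "Fixed effects will include treatment group (experimental vs. control), assessment time, the treatment-by-time interaction, and baseline values of the outcome as a covariate". It adds a covariance structure whose stated purpose is correlation across one participant's repeated measurements. The primary endpoint is the between-group difference at six months, and secondary outcomes use equivalent models. For significance it says: "Statistical significance will be set at p < .05".

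The nesting appears once, in the same section, for the mediation analysis: "a multilevel SEM that accounts for the partially nested delivery subgroups is reported as a sensitivity analysis". Of the power simulations, the Sample size section says: "These simulations incorporated baseline adjustment, within-subject correlation, and missing data patterns consistent with behavioral interventions". Clustering is not among the listed components; detailed parameters are left to the SAP.

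**The concern.** Women who share a room, a facilitator and a deliberately cultivated group climate for six sessions may respond alike. If they do, the experimental arm carries less independent information than its head count suggests, while the control arm is unaffected. A model that knows only about correlation within a person counts every experimental participant as a separate piece of evidence.

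The p-value and confidence interval of the single primary contrast would then be too optimistic, as would those of each secondary MMRM. A positive result could partly reflect a few effective groups or facilitators. The article acknowledges the nesting, yet accounts for it only in a secondary analysis and not in the one that decides the trial.

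**Working it through.** **Inputs from the article.** Target 196, so 98 per arm; attrition about 20%, so 98 × 0.80 ≈ 78 per arm at six months; workshop groups of up to 15; alpha 0.05, taken as two-sided because 95% intervals are reported; d ≈ 0.20–0.30 in the power simulations.

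**Assumed inputs.** ICC of the baseline-adjusted six-month outcome within workshop groups: 0.01 to 0.10. Baseline-to-follow-up correlation for the power figure: r = 0.5. Equal group sizes.

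**Step 1. The plan's own figure.** The minimum of 164 rests on f = 0.10, "With a significance level of α = 0.05 and statistical power (1 − β) of 0.80" and "assuming two groups with three repeated measurements". For the within-between interaction, λ = f²·N·k/(1 − ρ), with k = 3 measurements and ρ = 0.5 assumed. At N = 164, λ = 0.01 × 164 × 3 / 0.5 = 9.84 with 2 and 324 degrees of freedom, giving power 0.805. At N = 162 it is 0.7998. So 164 is reproduced, and the calculation contains no clustering term.

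**Step 2. Number and size of groups.** 98/15 = 6.5, so at least 7 groups, with mean size 98/7 = 14. After attrition, 78/7 ≈ 11.1 are retained per group.

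**Step 3. Variance.** With m per group, the experimental-arm mean has its variance multiplied by 1 + (m − 1)·ICC, and the control-arm mean by 1. With equal arms:

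true variance / model variance = [2 + (m − 1)·ICC] / 2

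Example, m = 14 and ICC = 0.05: (2 + 0.65)/2 = 1.325, so the SE ratio is √1.325 = 1.151.

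**Step 4. Type I error.** True error = 2·[1 − Φ(1.96 / SE ratio)]. In the example, 1.96/1.151 = 1.703, giving 8.9%.

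| ICC | SE ratio, m = 14 | Type I error | SE ratio, m ≈ 11 | Type I error |
|---|---|---|---|---|
| 0 | 1.00 | 5.0% | 1.00 | 5.0% |
| 0.01 | 1.03 | 5.8% | 1.03 | 5.6% |
| 0.02 | 1.06 | 6.5% | 1.05 | 6.2% |
| 0.05 | 1.15 | 8.9% | 1.12 | 8.0% |
| 0.10 | 1.28 | 12.7% | 1.23 | 11.0% |

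A simulation of the baseline-adjusted six-month contrast (7 groups of 14 against 98 independent controls, 100,000 replicates per cell) gave 4.9%, 5.7%, 6.6%, 8.8% and 12.7% for the five rows without dropout. With 20% dropout it gave 5.1%, 5.6%, 6.2%, 7.9% and 11.2%.

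**Step 5. Understatement of the SE at ICC 0.05.** 1 − 1/1.151 = 13% with full groups; 1 − 1/1.120 = 11% with about 11 retained.

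**Step 6. Power at d = 0.30, 78 per arm, r = 0.5.** Ignoring the groups, the standardised effect is 0.30 / √(1 − 0.25) / √(2/78) = 2.163, and power is Φ(2.163 − 1.96) = 0.58. At ICC 0.05 with 11.1 per group, 2.163/1.120 = 1.93 and power is Φ(1.93 − 1.96) ≈ 0.49. With Satterthwaite degrees of freedom (about 16, from 6 between-group degrees of freedom in one arm and 77 in the other) it is about 0.44.

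**The case against.** The strongest reply is that this is a condensed article. The sentence quoted on the primary model lists fixed effects, where a random effect would not appear, and the SAP is cited for full detail. The authors plainly know about the nesting, so the SAP may already handle it. This limits what can be said about the plan as a whole, but it does not rescue the article: besides the fixed effects, the article says what the covariance structure is for, and it mentions nesting only for mediation. On the power simulation the reply is stronger. A reader might infer that clustering was certainly left out, but the parameters are deferred to the SAP; all that can be said is that the listed components do not include it.

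A second reply is that no ICC is given and the primary contrast comes six months after the last shared session, so the residual correlation may be small. That stands. A reader might infer that the type I error exceeds 5% outright; the documents do not support this. At ICC 0 nothing happens, and near 0.01 the excess is under one percentage point. Individual randomization also protects the test under a strict null of no effect on anyone. The inflation concerns the null of no average effect when groups or facilitators differ in what they achieve.

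A reader might also infer that the multilevel model should become the primary mediation specification. With about 7 clusters, all in one arm, between-cluster variance is poorly estimated, and a single-level model with a disclosed multilevel sensitivity analysis is defensible for a non-primary analysis.

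**Conclusion.** The point holds in conditional form. The model in the article does not match the partially nested design that the article itself describes, and the resulting error is anti-conservative whenever six-month outcomes correlate within workshop groups. It reaches the primary contrast and every equivalent secondary MMRM.

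Over the assumed ICC range of 0.01 to 0.10, the nominal 5% test has a true error between about 5.6% and 12.7%. At ICC 0.05 the loss of power falls on a design whose authors already call its power moderate. These sizes rest on the assumed ICC, on 7 equal groups and, for power, on r = 0.5. They describe the article's model; whether the SAP differs could not be checked.

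**What to change.** In the primary and secondary MMRMs, add a random effect for delivery subgroup in the experimental arm only, treating each control as her own unit, and use Kenward-Roger or Satterthwaite degrees of freedom because there may be only about 7 groups. Keep the present model as a sensitivity analysis. Add an ICC range to the power simulation and report power across it. Leave the mediation specification as it is. If the SAP already contains these elements, change only the article's description of the primary model so that the two agree.

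The cost is wording in the article and SAP plus one subgroup identifier in the dataset. Intervals will be wider and degrees of freedom fewer. Subgroup identifiers also reveal which coded arm is experimental, so the analysis script should be written and locked on dummy data before the blinded analysts receive them. The article says recruitment has not begun, so the change can be made before any data exist.
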